##### Allocation concealment mechanism

The allocation concealment is through the sealed envelope system to conceal the sequence until the interventions are assigned. The sequence is generated and sealed by the PI. All investigators are blinded to the allocation.

#### Blinding (masking)

Masking**:** All participants, care providers/parents, all investigators, and outcomes assessors will be blinded. All genders will be included. Unbinding of the allocation will not occur until the analysis is complete.

#### Adherence

Adherence to the protocol will be measured by the number of capsules remaining at Week 8, as counted by the researcher. No participants will be excluded based on incomplete adherence to the protocol. Sensitivity analyses to control for variations in adherence will be controlled for in the analysis. Participants that seek other treatment at any stage during their involvement in the trial will be classified as treatment failures in the analysis.

#### Screening

Once a parent, guardian or child has shown interest in the trial via contacting the researchers, an explanation of the clinical trial and what is involved in participation initially occurs over the phone. The researcher will email, post, or direct the parent to the clinical trial website where they can download a copy of the Participant Information Sheet to read independently. The parent will be encouraged to discuss the participation with the child themselves and someone else who is able to support them in making their decision.

A follow up phone call or email will occur several days to a week later to verify the parent has read the information and discussed it with their child. This is an opportunity for further questions by the parent if needed. During this phone call the researcher will ask the parent if they would like their child to participate in the trial. If the parent says yes, the researcher will use the screening tool i.e. Participant screening procedure form (Universal), to determine eligibility in accordance with the defined eligibility criteria. All eligibility details collected through the screening process and before enrolment will be based on parent report of existing diagnoses rather than evaluation from an urologist or paediatrician. If the child is eligible an appointment date and time will be created for the participant and parent to attend the clinical trial site.

#### Assessments

Outcomes will be assessed by a *Case Report Form*, the *Paediatric Quality-of-Life Questionnaire (PinQ)*, and a *Participant Diary*.

##### Case report form

The Case Report Form (CRF) will be completed by the researcher at weeks 0, 2, 4, 6, 8, 16, 24, and 32. The baseline data collection will include demographic data, height and weight measurement, medications including complementary and over the counter medicines they are taking, medical history, risk factors for NE, prior treatments for NE, continence history, fluid intake per day. There is ongoing data collection fortnightly of any adverse events or concomitant medication via phone call or clinic visit whilst taking the intervention. As part of the CRF, a quality of life questionnaire (PinQ) will be completed by both the participant and parent/guardian at baseline, week 4, 8 and 32. The quality of life questionnaire chosen is the Paediatric Quality of Life Questionnaire (PinQ).

##### Paediatric quality-of-life questionnaire (PinQ)

The impact of NE on the child’s quality of life will be measured by the PinQ (Paediatric quality-of-life questionnaire) [13]. The PinQ is a tool used to measure urinary incontinence Quality of Life in children with voiding dysfunction. It has been reliably tested and validated in numerous trials since its conception [2, 14, 39]. Permission has been granted from the author for its use in this trial.

The PinQ will be completed by both parent and child on separate data collection forms as it has been shown that there has been inconsistencies in proxy and child answers when filling in the questionnaire [13]. It is completed by both parent and child as prior research has highlighted differences in reporting with proxy and self-reporting in the same questionnaire [14]. Children as young as 5 years old have been shown to reliably and validly self-report on their health-related quality of life in questionnaires when given the opportunity with an age-appropriate instrument [40]. If a child is unable to complete a questionnaire due to lack of cognitive or communicative development, the researcher will assist the child in developmentally appropriate language to complete the questions rather than the parent influence the response. The PinQ will be completed by both parent and child at Baseline, Week 4, Week 8 and finally in Week 32.

##### Diary

The daily diary for the first 8 weeks will constitute questions covering three main areas: compliance, fluid intake, and continence. There will be the option for the participant to complete it as an electronic diary or as a paper based one. This is for ease of the participant in their own environment. In the case of the electronic diary, the researcher will set up a widget on the parent’s smartphone. This is a link that takes the participant directly to their individual eDiary (which is identical to the paper one) where the parent is required to fill it in daily. Each participant will have an individual link which is linked to their own data within the online survey platform (Survey Gizmo). From week 9 to week 32, a weekly diary entry instead of daily will be required to record any weekly events of nocturia. This will be made available as an eDiary or a paper-based diary depending on the parent/guardian.

#### Statistical methods

All data will be analysed on STATA©14. Analyses will be conducted on an intention to treat basis. Descriptive and inferential statistics will be conducted. The difference in change between groups will be analysed using paired T-tests and Analysis of Variance (ANOVA). Groups will be compared at baseline and if difference(s) is/are ascertained, the variable(s) will be entered into the regression model to appropriately adjust the analyses. Sensitivity analyses will also be conducted to account for incomplete adherence to protocol. Interim statistical analysis for safety will occur after 30 participants have completed. This is same timing as the re-evaluation of the sample size calculation. All baseline, demographic, safety and efficacy outputs data will be summarised by treatment group. In summary tables of continuous variables, the minimum and maximum statistics the arithmetic mean and median, the 95% confidence interval, standard deviation, and standard error will be presented to the same number of decimal places as the original data. Safety outputs will be documented at the interim analysis and end of trial in columns with number, severity, treatment group and percentage. All hypothesis testing will be carried out at the 5% (2-sided) significance level unless otherwise specified. *P* values will be rounded to three decimal places. *P* values less than 0.001 will be reported as < 0.001 in tables (Table 1).

**Table 1 Tab1:** Details of the active and control interventions

Arms	Assigned Interventions
Active Comparator: Treatment 1 capsule in the morning (≤40 kg) or 2 capsules in the morning (> 40 kg) for 8 weeks duration.	Dietary supplement: Bedtime Buddy Active treatment- Proprietary combination of 420 mg of herbs. expressed as dry herb equivalent: Crateva nurvala 3000 mg (120 mg) *Equisetum arvense* 1500 mg (150 mg) Lindera Aggregata 1500 mg (150 mg)
Control Comparator: Placebo 1 capsule in the morning (≤40 kg) or 2 capsules in the morning (> 40 kg) for 8 weeks duration.	Placebo- Identical vegetarian capsule containing colour-matched cellulose to that of the active treatment

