##### Trial design

This is a randomised, prospective, double-blind randomised, placebo-controlled trial in which participants, researchers and statisticians analysing the data are blinded to which group the participants are randomised. It is a parallel group or non-crossover study. The allocation ratio is 1:1.

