#### Outcomes

##### Primary outcome

**Frequency of nocturnal enuresis (Week 8)**

The primary outcome for this study will measure efficacy as quantified by the change from baseline in the frequency of nocturnal enuresis at week 8. Parents are completing a daily diary (see Fig. 3) online or via hard copy which measures episodes of nocturia (waking wet through the night, and / or waking wet in the morning). The diary also captures the volume of fluid consumed in the day, together with the compliance of taking the capsule each day.

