#### Sample size

To detect a difference between the intervention group and the control group, a calculation from a trial on desmopressin and oxybutynin [38] was conducted. The power calculation used 80% power for 5% significance based on three-month results (*p* = 0.001). This resulted in the number of children required to recruit being 80 participants. This allows for a 20% attrition rate which provides an adequate number of participants in the primary analysis.

Due to the absence of existing studies involving similar populations and interventions, an interim sample size calculation will be conducted to confirm and potentially readjust the sample size as appropriate. The recalculation of the sample size will be conducted after 30 participants have completed the trial. The difference in the change (from baseline) in the frequency of nocturnal enuresis at week 8 will be calculated. This difference will then be imputed into the same equation used for the sample size calculation applied during study design. Any readjustment on the trial recruitment numbers will be resubmitted to the authorising HREC committee with the interim sample size calculation.

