### Methods: assignment of interventions

A block randomisation allocation was used based on 10 blocks of eight with an allocation of 1:1. Two extra blocks of eight were generated for over 80 allocations.

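### Paired t-tests are named alongside ANOVA for the between-group comparison of change, but in this parallel-group trial they can only describe change within an arm

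*Protocol article*

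**What the plan says.** The Statistical methods section of the protocol article gives one sentence on how the arms are compared: "The difference in change between groups will be analysed using paired T-tests and Analysis of Variance (ANOVA"). The same section sets the error rate: "All hypothesis testing will be carried out at the 5% (2-sided) significance level unless otherwise specified". It adds that the groups will be compared at baseline and that any variable found to differ will enter a regression model.

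The design is described under Trial design: "It is a parallel group or non-crossover study", and "The allocation ratio is 1:1". Under Methods: assignment of interventions, "A block randomisation allocation was used based on 10 blocks of eight with an allocation of 1:1". The article describes no matching of children across arms, and it states that there is no stratification.

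The primary outcome is efficacy "quantified by the change from baseline in the frequency of nocturnal enuresis at week 8". The Sample size section says what the trial is sized for: "To detect a difference between the intervention group and the control group".

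**The concern.** The sentence on the comparison names its own target, the between-group difference in change, and then attaches to it a test that cannot address that target. A paired t-test needs two measurements that belong together. Here those are the baseline and week-8 values of the same child, so the test answers whether children in one arm changed. Pairing an active child with a placebo child would be arbitrary, because nothing in the allocation links them.

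Children enter with at least three wet nights per week, so some regression to the mean is plausible. The Background reports that parents regard enuresis as developmental. Some fall in wet nights could therefore occur in both arms without any effect of the product, and separating that fall from a product effect is the purpose of the placebo arm. The Hypothesis section states that the product will reduce enuresis and names no comparator, so a significant paired test in the active arm could look like confirmation of it.

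**Working it through.** **1. What the design allows.** There are two independent arms, allocated 1:1 in blocks of eight, with no matched pairs. Let D be a child's change from baseline to week 8.
- Paired t-test in one arm: t = mean(D) / (SD(D)/√n). It tests whether the mean change in that arm is zero. The other arm does not appear in the formula.
- Two-sample t-test or two-group one-way ANOVA on D: it tests whether mean D is equal in the two arms. The two are the same test. On one simulated data set both gave p = 0.1146.

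Only the second addresses the comparison that the trial is sized for.

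**2. The plan's own figure.** The Sample size section gives 80 children including 20% attrition, at 80% power and 5% significance. It states no effect size, SD or response rate, so 80 cannot be reproduced. It is consistent with 80 × (1 − 0.20) = 64 evaluable, or 32 per arm. The point here does not depend on how 80 was reached; only the 32 per arm is carried forward.

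**3. Error rates if within-arm tests were used to judge efficacy.** Assumptions, none of them in the documents: no treatment effect, normally distributed change, and the same mean improvement of m SDs of change in both arms. The level is 5% two-sided, from Statistical methods.

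The power p of each paired test comes from the noncentral t distribution with 31 degrees of freedom and noncentrality m√32, with critical value 2.04. The arms are independent, so the probability of active significant and placebo not significant is p(1 − p).

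| Common improvement m (SD of change) | Active-arm paired test significant | Active significant, placebo not |
|---|---|---|
| 0 | 5% | 5% |
| 0.2 | 20% | 16% |
| 0.3 | 38% | 23% |
| 0.375 | 54% | 25% |
| 0.5 | 78% | 17% |
| 0.8 | 99% | 1% |

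Example at m = 0.5: 0.5 × √32 = 2.83, p = 0.782, and 0.782 × 0.218 = 0.170. If the SD of change were 2 nights per week, m = 0.375 would be a fall of 0.75 nights and m = 0.5 a fall of 1 night.

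Simulation of 20,000 trials at each of m = 0, 0.2, 0.3, 0.5 and 0.8 agrees. In the same simulations, with 32 or 40 per arm, the two-sample test (equivalently ANOVA on change) rejected in 4.8% to 5.3% of trials whatever the common improvement.

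**4. Baseline adjustment.** Let r be the correlation of baseline with week 8, and k the ratio of baseline SD to week-8 SD. The variance under ANCOVA relative to change-score ANOVA is (1 − r²) / (1 + k² − 2rk).
- r = 0.5, k = 1: 0.75 / 1.00 = 0.75.
- r = 0.5, k = 0.6: 0.75 / 0.76 = 0.99.

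The entry floor of three wet nights per week restricts the baseline spread but not the week-8 spread, so k below 1 is plausible. The gain in precision may be useful or negligible, and the documents do not allow it to be fixed.

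**The case against.** The strongest reply is that the same sentence also names ANOVA, so the plan does contain a valid between-group test with the right error rate. A natural reading of a condensed article is that paired tests describe change within each arm and ANOVA compares the arms. This stands in part: the trial is not left without a valid analysis. But the text does not divide the roles that way. It assigns both tests to the between-group difference, and that is a wrong statement rather than a detail left to the analysis plan.

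A reader might also infer that the trial will declare efficacy when the active arm is significant and placebo is not, with a false-positive rate of 25%. The documents do not support this. No section sets such a decision rule, and the Sample size section aims at intervention versus control. The 25% is also the ceiling of p(1 − p), reached only when each paired test has about 50% power. The table shows the pattern at about 1% when the common improvement is 0.8 SD, although the active-arm test alone is then significant in about 99% of null trials.

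A third inference would be that change-score ANOVA is itself invalid, or that ANCOVA is worth a stated number of extra children. Neither holds. Unadjusted ANOVA on change is valid under randomisation, and the gain from ANCOVA depends on r and k, which the documents do not give.

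**Conclusion.** The point holds as an error in the wording of the primary comparison. One of the two named tests cannot compare Urox with placebo in this design; the other can. The harm is conditional: it arises only if within-arm results are used to judge efficacy. In that case, with no treatment effect, 32 evaluable per arm and an assumed common improvement of 0.2 to 0.5 SD of change, a significant active-arm result appears in about 20% to 78% of trials, and the pattern of active significant and placebo not significant in about 16% to 25%, against about 5% for the between-group test. The common improvement and the SD are assumptions. The mismatch between the paired test and the parallel-group design rests on none.

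**What to change.** Remove paired t-tests from the sentence on the between-group comparison and limit them to description of change within each arm. State that the primary test is a between-group comparison of week-8 frequency of nocturnal enuresis, reported as the between-arm difference with its 95% CI. ANCOVA with baseline wet nights as covariate is preferable. The covariate should be fixed in advance, in place of the present rule under which a variable enters only if the groups are found to differ at baseline. An ANOVA or two-sample t-test on change would also be valid. No equivalent sample size should be claimed for ANCOVA.

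The cost is one sentence in Statistical methods, carried into the statistical analysis plan before unblinding. It needs no new data and no change to the planned 80 children.

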#### Allocation

##### Sequence generation

A computer-generated number randomisation was utilised: https://www.random.org/. No stratification was implemented due to the specified age restriction of ages 6–14. The block randomisation sequence generated is provided in a separate document that is unavailable to those who enrol participants or assign interventions.

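### Covariates are chosen by whether the arms happen to differ at baseline, so baseline wet nights will usually go unadjusted and power is given away

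*Protocol article*

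**What the plan says.** The primary endpoint is the "change from baseline in the frequency of nocturnal enuresis at week 8" (Outcomes, Primary outcome). The Statistical methods section gives the analysis: "The difference in change between groups will be analysed using paired T-tests and Analysis of Variance (ANOVA"). It then gives the covariate rule: "Groups will be compared at baseline and if difference(s) is/are ascertained, the variable(s) will be entered into the regression model".

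No section names baseline wet nights, or any other variable, as a covariate that is always in the model. No criterion for a baseline difference is stated. The nearest is the general rule in the same section: "All hypothesis testing will be carried out at the 5% (2-sided) significance level unless otherwise specified".

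The candidate list is long. Under Case report form, "The baseline data collection will include demographic data, height and weight measurement", followed by medications, medical history, risk factors, previous treatment, continence history and fluid intake. The design does not balance any of these: "No stratification was implemented due to the specified age restriction" (Sequence generation).

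**The concern.** A comparison of randomised arms at baseline measures the luck of the allocation. It does not show whether a variable predicts week-8 wet nights, which is the only good reason to adjust for it. A prognostic variable that is mildly imbalanced is left out, and an irrelevant one that is clearly imbalanced is let in.

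The variable that matters most for a change-score endpoint is the baseline count. Subtracting it does not adjust for it. Unless the baseline to week-8 correlation is 1, change stays negatively correlated with baseline, so an arm that starts higher by chance tends to show more improvement without any treatment effect. ANCOVA removes this; the stated rule does so only when the imbalance is large enough to be noticed.

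At stake are the precision of the primary comparison in a trial of 80 children, the reliability of the estimate when an imbalance goes unnoticed, and a primary model that is known in advance.

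**Working it through.** **The plan's own figure.** The Sample size section says "The power calculation used 80% power for 5% significance based on three-month results" and refers to "a calculation from a trial on desmopressin and oxybutynin", but gives no effect size, SD or response rates, so 80 cannot be reproduced. Only the attrition step can be checked: 80 × 0.80 = 64 evaluable, or 32 per arm at 1:1, and 64 / 0.80 = 80.

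**Inputs from the protocol.** 32 evaluable per arm, two-sided 5%, 80% power.

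**Assumptions not in the protocol.** A baseline difference means p < 0.05 on a t-test. Data are normal, with equal SD at baseline and week 8. The baseline to week-8 correlation r is 0.3, 0.5 or 0.7. The between-arm analysis is a comparison of mean change. In the simulation, baseline wet nights is the only candidate covariate.

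**Detectable effect.** Solving the two-sample t-test power equation for 32 per arm gives 0.71 SD of change (0.70 by the normal approximation, 2.80 × √(2/32)).

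**Largest imbalance that goes unflagged.** t(0.975, 62) × √(2/32) = 1.999 × 0.25 = 0.50 SD.

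**Shift in the estimate at that limit.** A baseline imbalance of d SD moves the expected change difference by (1 − r)d in outcome SDs. The SD of change is √(2(1 − r)). The shift in SDs of change is therefore d × √((1 − r)/2).

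**Variance.** Against the unadjusted change score, ANCOVA leaves a fraction (1 − r²)/(2(1 − r)) = (1 + r)/2, that is 0.65, 0.75 and 0.85.

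**Simulation.** 32 per arm, at least 100,000 trials per setting. The stated rule (ANCOVA only if baseline p < 0.05, otherwise change score) is set against ANCOVA always. Power is taken at an effect of 0.71 SD of change.

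| r | Worst-case shift (SD of change) | Share of 0.71 | Type I error, rule | Power, rule | Power, ANCOVA always |
|---|---|---|---|---|---|
| 0.3 | 0.30 | 42% | about 4.0% | about 81% | about 93% |
| 0.5 | 0.25 | 35% | about 4.3% | about 81% | 89-90% |
| 0.7 | 0.19 | 27% | about 4.6% | about 81% | about 85% |

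ANCOVA always holds type I error at 5.0%. Never adjusting gives 80% power, so the rule recovers only about one point.

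**How often it bites.** Baseline wet nights is flagged in about 5% of trials. An imbalance above 0.3 SD goes unflagged in about 18%. Normal check: 0.3/0.25 = 1.2 and 0.5/0.25 = 2, so 2[Φ(2) − Φ(1.2)] = 18.5%. Within those trials the false-positive rate of the change-score test is about 9%, 8% and 7% for r = 0.3, 0.5 and 0.7.

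**Typical size.** The mean absolute unflagged imbalance is about 0.18 SD. The same formula gives a shift of 0.11, 0.09 and 0.07 SD of change, or 15%, 13% and 10% of 0.71.

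**Chance selection.** With k independent candidates each tested at 5%, the chance that at least one is flagged is 1 − 0.95^k: 23% for k = 5, 40% for k = 10, 54% for k = 15.

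**The case against.** The best defence is that the rule does little harm on average, and much of that stands.

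- **Error rate.** A reader might infer that choosing the model from the data makes the 5% level and the confidence interval invalid. The calculations do not support that. Overall type I error is slightly below 5%, because unadjusted tests are conservative in the many trials where baseline is close to balanced. Inflation appears only in the minority with a moderate, unflagged imbalance.
- **Bias.** Over all randomisations the change-score estimate is unbiased. The shift is conditional on the imbalance that occurred, and the figures at 0.50 SD are a worst case; the typical shift is about a third of that.
- **Baseline is used.** The endpoint subtracts it. What is missing is adjustment.
- **No test is stated.** The protocol speaks only of comparing the groups and finding differences, so the 5% test is a reading, supported by the section's general 5% rule. If judgement is meant instead, the model still depends on chance imbalance and is harder to reproduce.
- **No stratification.** A reader might count this as a second error. It is a design choice; it means only that the design does not protect baseline frequency.
- **Blinding.** The analysing statisticians are blinded, which limits deliberate selection but does not stop chance from choosing the covariates.

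A separate analysis plan could hold more detail. The rule is nevertheless stated in the protocol and would have to be withdrawn there.

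**Conclusion.** The point holds as a loss of efficiency and of pre-specification. It does not make the trial's inference invalid. Following the protocol as written gives up about 4 to 12 percentage points of power for the primary comparison (81% against 85-93%). It also leaves roughly one trial in six with an unflagged imbalance that raises the false-positive rate to about 7-9%, and it fixes the model only after the data are seen.

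The sizes rest on the assumed 5% baseline test, normal data, r of 0.3 to 0.7 and 32 evaluable per arm. The direction does not depend on the exact r: (1 + r)/2 is below 1 for any correlation below 1, apart from the one degree of freedom spent. The change should be made, but the trial does not stand or fall by it.

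**What to change.** Delete the compare-then-adjust sentence. In its place, state that week-8 frequency of nocturnal enuresis (or its change from baseline, which gives the same treatment estimate) will be analysed by ANCOVA, with treatment arm and baseline wet nights per week always in the model whatever the observed balance. State also that baseline comparisons will not be used to select covariates. Any further covariate, such as age, is optional and must be named before unblinding.

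The cost is wording and one degree of freedom. The Case report form section does not expressly list a wet-nights count at baseline, and the diary is first explained at the Week 0 visit. The fix nevertheless needs no baseline value beyond the one that the change-from-baseline endpoint already requires.
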